## Abstract

**Background::**

Knee osteoarthritis (KOA) is a common degenerative joint disorder that affects 250 million people globally. KOA can lead to disability and is often associated with cardiovascular disease, poor quality of life, and mortality. The most common treatment for KOA is non-steroidal anti-inflammatory drug administration. However, the analgesic effect is limited and often accompanied by multiple side effects. Hence, many KOA patients opt for complementary and alternative medicine. Acupuncture is one of the most popular complementary treatments with great analgesic effect and minimal side effect. Electroacupuncture (EA) and laser acupuncture (LA) have been known to reduce pain in KOA patients. However, to date, no study has assessed the benefits of combining these two therapies.

**Methods::**

Fifty participants diagnosed with KOA, aged 50 years or older, and with consistent knee pain for more than 3 months were recruited and randomly assigned to the treatment group (EA plus LA) or control group (EA plus sham LA without laser output). All subjects in the treatment group will undergo a combined EA and LA treatment thrice a week for 4 weeks. The acupuncture will be performed on GB33, GB34, SP9, SP10, and ST36 sites. The treatment group will receive acupuncture with a transcutaneous electrical nerve stimulator at GB33, GB34, SP9, and SP10 sites and with LA at EX-LE5, ST35, and BL40 sites. The subjects in the control group will undergo the same treatment modality as the treatment group, except these subjects will not be exposed to laser output. Outcome measurements will include visual analog scale, Western Ontario McMaster Universities Osteoarthritis Index, Knee injury and osteoarthritis outcome, body composition analysis, knee range of motion, quadriceps muscle stiffness, one-leg standing with eyes open test, and the 30-s chair stand test before and after 4 weeks of intervention.

**Objectives::**

This protocol aims to investigate the combined effect of EA and LA in KOA patients.

## Introduction

1

Knee osteoarthritis (KOA) is a common degenerative joint disorder that primarily affects elderly adults.^[1]^ Approximately 250 million people are affected by KOA globally, and this number is expected to increase in the future.^[2]^ KOA symptoms include knee stiffness, arthralgia, and limitation in range of motion, which can lead to a decrease in quality of life and even disability in severe cases.^[3,4]^ A previous study showed that KOA also affects the structure of the knee joint.^[5]^ Synovial inflammation, abnormal bone structure, and bone marrow lesions are commonly observed in KOA patients, which could be the underlying cause of persistent knee pain.^[5]^ Among contributors to global disability, KOA ranks 11th, and some of its secondary diseases include obesity, cardiovascular disease, and leading to higher mortality.^[6]^

The modality of KOA treatment depends on the severity of its clinical symptoms. Currently, non-pharmacological interventions such as exercise and weight loss are the main treatment modalities for mild KOA.^[7]^ In cases when such non-pharmacological interventions are inadequate, patients are often treated with topical non-steroidal anti-inflammatory drugs (NSAIDs).^[8]^ In moderate to severe cases, the treatment modalities include exercise,^[9]^ knee braces,^[10]^ walking aids,^[11]^ oral NSAIDs,^[12]^ and surgery.^[13]^ Oral NSAIDs are commonly used medicine to alleviate KOA-associated pain; however, long-term use of NSAIDs is often associated with cardiovascular diseases such as myocardial infarction, kidney injury, and gastrointestinal symptoms such as gastrointestinal bleeding.^[14,15]^ Therefore, alternative treatment modalities to alleviate KOA symptoms are in high demand. Non-pharmacological KOA intervention includes exercise, heat and cooling packing, neuromuscular electrical stimulation, transcutaneous electrical nerve stimulation, low-level laser therapy (LLLT), massage, and acupuncture.^[16]^ The exercise programs emphasize on improving aerobic capacity, quadriceps muscle strength, and lower extremity performance.^[17]^

Acupuncture is one of the most popular treatment modalities to alleviate KOA symptoms. Transcutaneous electrical nerve stimulation and acupuncture have similar mechanisms to relieve pain without serious adverse effects.^[18]^ Electroacupuncture (EA), a combination of acupuncture and transcutaneous electrical nerve stimulation, has become a popular treatment for KOA and is associated with a low risk of adverse reaction.^[19–21]^

Laser acupuncture (LA), a form of LLLT, is painless, non-invasive, has no risk of infection, and can be combined with traditional acupuncture.^[22,23]^ Currently, LA is primarily used to address arthralgia or muscular pain.^[24,25]^ LLLT has been reported to be a cost-effective analgesic therapy.^[26]^ However, the benefits of LA in alleviating KOA symptoms have remained elusive. In one previous clinical trial, LLLT has been suggested to alleviate KOA symptoms by increasing and decreasing serum beta-endorphin and substance P levels, respectively.^[27]^ Some studies analyzing the effect of LLLT in KOA patients produced ambiguous results. A meta-analysis on these studies conducted by Stausholm et al^[28]^ showed that LLLT can reduce pain and address disability in KOA patients. A randomized controlled trial conducted by Alghadir et al showed that LLLT was effective in reducing knee pain intensity at rest and movement, function, and ambulation. Therefore, LLLT seemed to be an effective modality for short-term pain relief and function improvement in patients with chronic knee OA.^[29]^

To date, there are no studies on the effect of a combined application of EA and LA in KOA patients. We will conduct a two-arm parallel clinical trial. This study aims to investigate the effect of a combined application of EA and LA and explore the effects of LA in terms of knee pain, knee range of motion, knee stiffness, and quadriceps strength and function in KOA patients. We hypothesize that a combination of LA and EA will produce more beneficial results than the application of these therapies alone in addressing KOA symptoms.

## Methods

2

### Ethics approval

2.1

The study was approved by the Human Ethics Committee of Chang Gung Medical Foundation Institutional Review Board, IRB No. 201901018A3C501. All participants will provide written informed consent before their enrollment in this study. Personal information will be collected, shared, and maintained in an independent closet to protect confidentiality before, during, and after the trial. The protocol has been registered at ClinicalTrials.gov (Identifier: NCT04188925).

### Study design

2.2

This randomized controlled trial will be conducted at the Department of Chinese Medicine at the Kaohsiung Chang Gung Memorial Hospital from August 2019 to December 2020. The participants recruited from our outpatient departments will be randomly allocated to the treatment group (LA plus EA, n = 25, expected) or the control group (sham LA without laser output plus EA, n = 25, expected). All participants will receive 12 sessions of treatment over 4 weeks. The study design is depicted in Figure 1.

**Figure 1 F1:**
[figure not shown]
Flowchart of the trial. KOOS = Knee injury, and osteoarthritis outcome, VAS = Visual analog scale, WOMAC = Western Ontario McMaster Universities Osteoarthritis Index.

### Participants

2.3

The diagnosis of KOA depends on the patient's history (age more than 50 years old, persistent knee pain, limited morning stiffness, reduce function, crepitus, restricted movement and bony enlargement)^[30]^ and radiography (osteophytes formation, joint space narrowing, subchondral bone sclerosis, and subchondral cysts).^[31]^ In this study, we recruited patients who were diagnosed with KOA, aged more than 50 years old and had knee pain for more than 3 months. Designated physicians evaluated the eligibility of all participants. Patients’ inclusion criteria for this study were based on the following factors: visual analog scale (VAS) > 3 points in daily activity, Kellgren–Lawrence Grading Scale grade is between 1 and 3 on knee X-ray, and informed consent obtained adequately. Patients’ exclusion criteria for this study were based on the following factors: history of knee arthroplasty, traumatic injury related joint deformity, body mass index more than 35, pacemaker insertion, photosensitivity, intra-articular injection or acupuncture 1 month before the enrolment, and any factors that may affect the evaluation of the outcome, such as psychiatric disorder and moderate to severe mental retardation.

### Sample size and randomization

2.4

The necessary sample size was calculated from the result of a previous study on the effect of LLLT. In this study conducted by Al Rashoud et al, the mean difference (standard deviation) of the VAS at the baseline before the treatment were 6.4 (1.9) at the treatment group, and 5.9 (1.8) at the control group, and the mean difference (standard deviation) of the VAS after completing the treatment were 3.2 (1.7) at the treatment group, and 3.8 (2.3) at the control group.^[32]^ We aimed to achieve an effect size of 0.569, a significance level (α) of 0.05, the desired power (1 − β) of 0.80, and correlation among repetition measures of 0.5, and as such, the estimated sample size for this study was 22. Anticipating a 20% dropout rate, a total of 50 participants were recruited.

We used a randomized block design to distribute participants equally into two groups, A and B, with the help of a research randomizer (https://www.randomizer.org). Designated physicians enrolled participants who met the inclusion criteria and grouped the participants according to the result of randomizer by the website. The trial participants, outcome assessors, and data analyst will be blinded after assignment to interventions using labels A and B for the 2 groups.

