Among many of the mechanisms of KOA, synovial inflammation (synovitis), abnormal bone structure, osteophytes, and bone marrow lesions can result in knee pain.^[5]^ It is possible that EA treatments could lead to activation of the nervous system and inhibition of inflammatory and neuropathic pain by desensitizing peripheral nociceptors and reducing pro-inflammatory cytokines.^[51]^ The clinical effects of LA are likely to encompass anti-inflammatory, neural modulation, cell healing and regeneration effects.^[23]^ Both LA and EA have anti-inflammatory and neural modulation, which may decrease knee pain in KOA. Conversely, exercise therapy can reduce knee pain in patients with KOA and these exercise therapies are focused on improving aerobic capacity and quadriceps muscle strength.^[17]^ LA has an analgesic effect and can improve the function and muscle strength of quadriceps in KOA.^[37]^ Besides, LA and EA have many advantages, including low risks of complications, pain, cost, and high analgesic efficacy. Although some studies confirmed such beneficial effects of LA or EA in improving KOA symptoms, the combined effect of EA and LA on KOA remains elusive.

In this study protocol, we will use LA at 6 J/acupoint delivered with an 810 nm laser in addition to EA treatment for 4 weeks. LA treatments are poised to heal damaged chondrocytes, which are more susceptible to pain stimulation.^[59]^ The outcome evaluations will include analyses of subjective symptoms, quadriceps muscle functions, and body composition measurements. In conclusion, we hypothesize that a combination of LA and EA is expected to be more effective than these therapies alone in alleviating knee pain and stiffness and increasing muscle strength of lower limbs, which can further improve the balance and quality of life. Moreover, this combined therapy may also benefit in reducing the need for total knee replacement therapy and further decrease the cost coverage of national health insurance.

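### The sample size borrows its effect from laser apparently given without electroacupuncture, so the 80% power is unsupported for what laser adds to electroacupuncture

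*Protocol article*

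**What the plan says.** Section 2.4 (Sample size and randomization) gives the origin of the effect: "The necessary sample size was calculated from the result of a previous study on the effect of LLLT". It quotes VAS means (SD) from that study of "6.4 (1.9) at the treatment group, and 5.9 (1.8) at the control group" at baseline and "3.2 (1.7) at the treatment group, and 3.8 (2.3) at the control group" after treatment. It continues "We aimed to achieve an effect size of 0.569", with "a significance level (α) of 0.05", power 0.80 and a correlation of 0.5 between measurements. The result is a sample size of 22, and 50 participants after allowing for 20% dropout.

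Section 2.2 (Study design) describes the comparator as "the control group (sham LA without laser output plus EA, n = 25, expected"). Section 2.5 (Intervention) gives EA in all 12 sessions to both arms. The Introduction states: "To date, there are no studies on the effect of a combined application of EA and LA in KOA patients". The Discussion cites a review in which at least 4 weeks of EA improved VAS. Of the two treatments it says: "Both LA and EA have anti-inflammatory and neural modulation, which may decrease knee pain in KOA".

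**The concern.** The trial compares EA + LA with EA + sham LA, so its estimand is the increment of laser over EA. The effect in 2.4 comes from laser against a control group. If no earlier study combined the two treatments, that control group did not have EA, whereas every control patient here does. The 1.1-point difference is then not an estimate of the increment over EA. It becomes one only if laser relieves as much pain on top of EA as it does without EA, and 2.4 does not say that it relies on this.

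The interpretation of a null result is at stake. If part of the effect is lost on top of EA, power is below the stated 80%. A non-significant difference could then be read as showing that laser adds nothing to EA, although the trial was never sized on an estimate of that increment.

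**Working it through.** **Inputs.** VAS means and SDs, the effect size 0.569, r = 0.5, alpha 0.05 and 20% dropout are from 2.4. The 25 per arm is from 2.2 and the 1.8-point MCID from 2.6. I assume a two-sided test. The share k of the source effect that remains on top of EA is not in the documents; I take 100, 75 and 50% as an assumed range, with the SD unchanged.

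**1. The plan's effect.**
- Difference in change: (6.4 − 3.2) − (5.9 − 3.8) = 3.2 − 2.1 = 1.1 points.
- SD of change at r = 0.5: treatment √(1.9² + 1.7² − 1.9 × 1.7) = √3.27 = 1.81; control √(1.8² + 2.3² − 1.8 × 2.3) = √4.39 = 2.10; pooled √((3.27 + 4.39)/2) = 1.957.
- 1.1/1.957 = 0.562. With the average of the four quoted variances, 1.1/1.938 = 0.567. The plan's 0.569 thus matches a standardized mean difference.

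**2. The plan's sample size.** A repeated-measures ANOVA, between-group factor, two groups and two measurements, with 0.569 entered as Cohen's f, has λ = f² × N × 2/(1 + 0.5). At N = 22, λ = 0.3238 × 22 × 1.333 = 9.50 and power is 83%; 22 is the smallest even total that reaches 80%. I take this as the plan's calculation, although 2.4 does not say whether 22 is a total.

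**3. Power over the assumed range.** For a two-group t test of VAS change, the noncentrality is k × 0.569 × √(n/2) with 2n − 2 degrees of freedom. A 20% dropout leaves 50 × 0.8 = 40, or 20 per arm.

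| Calculation | k = 100% | 75% | 50% |
|---|---|---|---|
| Two-group change, 25 per arm | 50% | 32% | 17% |
| Two-group change, 20 per arm | 42% | 26% | 14% |
| Plan's method (step 2), total 50 | 99.5% | 93% | 62% |
| Plan's method, total 40 | 98% | 86% | 53% |
| Plan's method, total 22 | 83% | 60% | 31% |

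At k = 100% the effects add fully and this point contributes nothing. The gap between 50% and 99.5% there comes from reading 0.569 as a standardized mean difference rather than as f, which is a separate issue. Only the decline along each row belongs here.

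**4. What 50 participants deliver, without any borrowed effect.**
- Detectable at 80% power: 0.809 SD with 25 per arm, 0.809 × 1.957 = 1.58 points; 0.909 SD with 20 per arm, 0.909 × 1.957 = 1.78 points.
- 95% CI half-width: 2.011 × 1.957 × √(2/25) = 1.11 points; 2.024 × 1.957 × √(2/20) = 1.25 points.

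Both detectable differences exceed the source study's 1.1 points and lie just below the 1.8-point MCID. With 25 per arm, an observed difference of zero would have an upper limit of 1.11, so a non-significant result that favours laser at all would not exclude even the full source effect.

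**The case against.** Both the source study and this trial compare laser with no laser. If the effects add, 0.569 carries over unchanged. With no earlier study of the combination, sizing on laser versus control is a usual choice, and a condensed article may leave the justification to a fuller document.

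A reader might infer that power is overstated because EA is in both arms. The documents do not support that. They give no effect of laser over EA. The Discussion's sentence on shared mechanisms is offered as a reason to combine the treatments, and the same section lists laser actions that it does not ascribe to EA, such as cell healing and quadriceps strength. The laser and the needles also use different acupoints. Nor can the 1.8-point MCID stand in for the effect of EA in order to derive a reduced increment: 2.6 gives it as a threshold for an effective treatment. If spread falls along with mean pain, the standardized effect need not shrink. On the plan's own method, 40 to 50 patients keep 86 to 93% power at 75% of the effect. That the source arms had no EA is itself an inference from the novelty statement.

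All of this stands, and it limits the claim to missing support. It does not remove the point. The article sets out the source, means, SDs and effect size as the basis for this trial, yet nothing in it ties them to the add-on comparison. The expectation that the combination beats either treatment alone fits a smaller increment as well as a full one. The reassurance from the plan's method also depends on reading 0.569 as f, which the quoted means do not bear out.

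**Conclusion.** The point holds in limited form. The effect in 2.4 is carried over from laser apparently without EA to a comparison in which both arms have EA, on an unstated assumption of full additivity. The 80% power is therefore unsupported for EA + LA versus EA + sham LA, and it may be overstated; the documents do not settle whether or by how much.

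If a quarter or half of the effect were lost, the two-group comparison of change would lose about 19 or 34 percentage points of power with 25 per arm (50 to 32 to 17%, from unrounded values of 50.5, 31.5 and 16.7). With 20 per arm it would lose about 16 or 28 (42 to 26 to 14%). These figures rest on the assumed range, an unchanged SD, and 0.569 as a standardized mean difference. The detectable differences rest on r = 0.5. At r = 0.3 the SD of change is 2.30 and the difference detectable with 25 per arm is 0.809 × 2.30 = 1.86 points; at r = 0.7 they are 1.53 and 0.809 × 1.53 = 1.24.

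**What to change.** In 2.4:
- State that the effect comes from laser versus control, apparently without EA, and that using it here assumes full additivity of laser and EA effects.
- Keep 50 participants. Replace the bare 80% claim with what that size delivers for a two-group comparison of VAS change, with an SD of change of about 1.96 at r = 0.5: a detectable difference of about 1.6 points with 25 per arm and 1.8 with 20 per arm, and a 95% CI half-width of about 1.1 to 1.25 points.
- Give power at 100, 75 and 50% of the source effect as an assumed range (50/32/17% with 25 per arm; 42/26/14% with 20 per arm). Note that the low value at 100% reflects how 0.569 is read and not the presence of EA.

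In 2.7 (Statistical analysis), add one sentence: a non-significant VAS difference will be reported with its CI against the 1.8-point MCID and not as evidence that laser adds nothing to EA.

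The cost is some rewording. No patients, visits or procedures are added. The stated power becomes less favourable.

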We will evaluate the frequency of analgesic used to treat knee pain after each intervention, including acetaminophen, a non-steroidal anti-inflammatory drug, or opioid drug. VAS will be used to evaluate the intensity of knee pain during activity and rest on a scale of 0 to 10, corresponding to the minimum and maximum discomfort intensity. The minimal clinical important difference (MCID) of VAS is 1.8 units,^[34]^ implying that an effective treatment will improve the VAS score by 1.8 points. WOMAC is a subscale for assessing the physical function of knee joints. There will be 17 questions with grading from 0 to 4 points for each question. Thus, the total score will be between the ranges of 0 to 68 points. Higher points correspond to more difficulties in performing a given activity. The MCID of WOMAC is 6 units.^[35]^ The KOOS is a self-administered scale and evaluates five outcomes, including pain, symptoms, activities of daily living, sport and recreation function, and knee-related quality of life. The scale is divided into five factions, including none, mild, moderate, severe, and extreme, which represent the severity of the deterioration of knee function and the impairment in daily living.^[36]^ A previous study showed that one-time LLLT had some effects on improving the knee function and muscle strength of quadriceps in KOA.^[37]^ We use Myoton-3 myometer and InBody 270 to measure muscle functions. In Myoton-3 myometer, the tip is placed on the midpoint of the patient's rectus femoris to measure muscle stiffness, representing the muscle ability to resist the changes of its shape, caused by external forces.^[38]^ InBody 270 can measure body composition, including the fraction of muscle and fat, and the muscle mass distribution of four limbs. This device will be used to evaluate the composition of thigh muscles and any possible muscle imbalance. One-leg standing with eyes open test will be used to assess balance and muscle strength of lower extremities.^[39]^ The patient will stand on one leg with their hands on hips and eyes opening for up to 120 s. We will record the time that the patient can stand on one leg under the instruction. Another functional assessment is the 30-s chair stand test, which can evaluate the muscle performance and the endurance of lower limbs.^[40]^ The patient will sit on the chair with bilateral feet stepping on the ground and hands crossed over the chest. Subsequently, the patient stands up and then sits down. Completing one standing up and then sitting down scores one, etc. We will calculate the number of times the patient can stand up and then sit down in 30 s. A designated study assistant will evaluate these tests.

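### Section 2.4's 80% power claim, effect size of 0.569, N of 22 and recruitment of 50 do not agree with each other or with the source data; for the effect behind them, power is about 42–50% (unadjusted change) or 53–62% (baseline-adjusted)

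*Protocol article*

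**What the plan says.** Section 2.4 (Sample size and randomization) bases the calculation on an earlier low-level laser study. It gives that study's VAS means (SD) as "6.4 (1.9) at the treatment group, and 5.9 (1.8) at the control group" at baseline and "3.2 (1.7) at the treatment group, and 3.8 (2.3) at the control group" after treatment.

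The inputs are then stated: "We aimed to achieve an effect size of 0.569", "a significance level (α) of 0.05", and a desired power "of 0.80, and correlation among repetition measures of 0.5". The result is that "the estimated sample size for this study was 22. Anticipating a 20% dropout rate, a total of 50 participants were recruited". The section does not say whether 0.569 is a d or an f, which test was sized, whether alpha is one- or two-sided, or whether 22 is a total or a per-arm number.

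Section 2.2 (Study design) expects 25 per group ("LA plus EA, n = 25, expected", and the same for control). Section 2.7 plans repeated-measures ANOVA and generalized estimating equations for changes between the groups. Section 2.6 lists VAS at rest and during activity, with analgesic frequency, as primary outcomes. On the 1.8-point minimal clinically important difference (MCID) it comments: "implying that an effective treatment will improve the VAS score by 1.8 points".

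**The concern.** An effect size of 0.569 on the d scale is moderate, and a two-arm trial with 80% power for it needs about 100 participants in total, not 22. On the f scale the same number is very large, equivalent to d = 1.14 (f = d/2 for two equal groups), and nothing in the quoted data supports that. Separately, no ordinary 20% dropout allowance leads from 22 to 50.

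At stake is how the result on a primary outcome is read. If the trial is described as 80% powered but has roughly an even chance, or a little better, of detecting the difference it was sized on, a null result could be taken as stronger evidence than it is that laser adds nothing to electroacupuncture.

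**Working it through.** **Inputs (all from section 2.4 unless noted).** Baseline VAS 6.4 (1.9) v 5.9 (1.8); post-treatment 3.2 (1.7) v 3.8 (2.3); effect size 0.569; alpha 0.05, taken here as two-sided; power 0.80; correlation r = 0.5; N = 22; dropout 20%; 50 recruited. Allocation is 25 per arm (section 2.2).

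**Step 1. Reproduce 22.** For a repeated-measures ANOVA, between-factors test, two groups and m = 2 measurements, the noncentrality is λ = N·f²·m / [1 + (m − 1)r], with f = 0.569.

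- N = 20: λ = 20 × 0.3238 × 2 / 1.5 = 8.63; power 0.794.
- N = 22: λ = 22 × 0.3238 × 2 / 1.5 = 9.50; power 0.834.

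The smallest equal-group total above 80% is therefore 22, matching the article. Other readings of 0.569 give different totals:

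| Calculation | N for 80% power |
|---|---|
| Group-by-time interaction, as f | 10 |
| One-way ANOVA, as f | 28 |
| Two-sample t, as d, two-sided | 100 |
| Two-sample t, as d, one-sided | 78 |
| Paired t, two-sided / one-sided | 27 / 21 |

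The one-sided paired test comes close, but it is not a comparison of two groups.

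**Step 2. Where 0.569 comes from.** Difference in mean change: (6.4 − 3.2) − (5.9 − 3.8) = 3.2 − 2.1 = 1.1 points. Three ways to standardise it:

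- Pooled SD of the four values: √[(1.9² + 1.8² + 1.7² + 2.3²)/4] = 1.938; d = 0.567.
- Mean of the four SDs: 1.925; d = 0.571.
- SD of change at r = 0.5: treatment √(1.9² + 1.7² − 1.9 × 1.7) = 1.81; control √(1.8² + 2.3² − 1.8 × 2.3) = 2.10; pooled 1.957; d = 0.562.

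The stated 0.569 lies within this range, so it behaves as a between-group d.

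**Step 3. Power at d = 0.569, unadjusted pre-post change.** Two-sample noncentral t, noncentrality d·√(n/2) with n per arm, two-sided 0.05.

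| Analysed | Noncentrality | Power |
|---|---|---|
| 40 (20 per arm) | 0.569 × √10 = 1.80 | 41.8% |
| 50 (25 per arm) | 0.569 × √12.5 = 2.01 | 50.5% |
| 98 (49 per arm) | 0.569 × √24.5 = 2.82 | 79.6% |
| 100 (50 per arm) | 0.569 × √25 = 2.85 | 80.4% |

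**Step 4. Baseline-adjusted analysis.** With equal variances and r = 0.5, the change-score variance is 2σ²(1 − r) = σ², and the adjusted variance is σ²(1 − r²) = 0.75σ². The effective d is 0.569/√0.75 = 0.657. Power is 52.6% with 40 analysed and 62.4% with 50; 80% needs 76 analysed.

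**Step 5. Dropout.**

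- 22 as a total: 22/0.8 = 27.5, so 28.
- 22 per arm: 44/0.8 = 55.
- Backwards: 50 × 0.8 = 40, below 44. Going from 44 to 50 covers only 1 − 44/50 = 12% dropout.

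**Step 6. What 50 participants can show on change.** At 20 per arm the 80%-power detectable difference is d = 0.91, or 0.91 × 1.94 to 1.96 ≈ 1.8 points. The expected 95% confidence interval half-width is t × SD × √(2/n): with SD 1.957, 2.011 × 1.957 × √(2/25) = 1.11 at 25 per arm, and 2.024 × 1.957 × √(2/20) = 1.25 at 20 per arm.

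**The case against.** **The swap of d for f is inferred.** This stands. The article names no index, test or software, and the quoted data give 0.562, 0.567 or 0.571 but never exactly 0.569. A reader might take the swap as a documented fact; it is only the explanation that best fits both 0.569 and 22. The power result does not depend on it, because the 1.1-point difference comes straight from the quoted means.

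**The 42–50% range depends on the analysis.** This also stands. Section 2.5 has VAS recorded after every session, and section 2.7 allows generalized estimating equations as well as ANOVA. Suppose 12 post-baseline measurements, SD 1.94, all correlations 0.5 and 20 to 25 per arm. A 1.1-point effect constant over all sessions would then give 66–76% power on mean change, or 90–95% with baseline adjustment. An effect growing linearly over sessions would give 25–30% or 42–50%. These are assumptions, not figures from the article. Its sizing uses only before-and-after data, which is why the two-timepoint comparison is the natural check. A flat statement that the trial is a coin flip would still go too far.

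**The dropout error has limited effect.** Largely right. If 22 is a total, 50 exceeds the 28 needed, so the step is unexplained rather than short. If it is per arm, which the article never says, completers fall from 22 to 20 per arm and power on change from 45% to 42%.

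**The design is unaffected.** True. The article says that 50 were recruited, and it contains no rule equating non-significance with no effect. The risk of misreading is therefore a reason to correct the justification, not evidence of a flawed analysis.

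**Conclusion.** The point holds as an error in the stated justification. The source data give a d of about 0.56–0.57, for which neither 22 nor 50 participants deliver 80% power in a two-timepoint comparison. Power with 50 recruited is about 42–50% for unadjusted change and about 53–62% with baseline adjustment. The lower figure of each pair is for 40 completers, the upper for all 50. Reaching 80% on unadjusted change would need 50 per arm analysed. The 20% dropout allowance does not connect 22 to 50 whether 22 is a total or per arm.

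These figures assume one VAS outcome at an unadjusted two-sided 0.05, r = 0.5 and the quoted SDs.

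A reader might also infer that the trial is adequately powered after all, because its 80%-power detectable difference at 20 per arm, about 1.8 points, coincides with the MCID in section 2.6. The article does not support that. It describes 1.8 points as an improvement under treatment, not as a difference from a control arm that itself receives active electroacupuncture. The only between-group difference obtainable from the article's sizing data is 1.1 points.

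**What to change.** Reword section 2.4, keeping 50 participants:

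1. Withdraw the claim of 80% power at 0.569.
2. Name the effect-size index and the test, and say whether N is a total or per arm.
3. Correct the dropout sentence. With 50 recruited and 20% lost, 40 are analysed (20 per arm).
4. Restate power for the 1.1-point difference under the named analysis: about 42–50% for unadjusted pre-post change, or about 53–62% if baseline-adjusted. If the session-by-session VAS values are to be used, state the assumed effect pattern and correlations.
5. Give the detectable difference of about 1.8 points at 20 per arm only as a sensitivity figure, not as a target justified by the MCID.
6. State that a non-significant result will be read through its confidence interval, with an expected half-width of about 1.1–1.25 points for unadjusted change.

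The cost is a less favourable stated power. No further enrolment and no change to treatment or outcomes are needed.
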